In 1979, a shortage of NICU nurses in Estonia prompted Levin [8, 9] to implement a “humane” care model in which parents provide nursing care for the infant (except for respiratory care and administration of intravenous [IV] fluid and medication), while nurses provide teaching and guidance to parents. In a non-randomised, before-after comparison, this model was associated with a 37 % improvement in weight gain in the first 20 days of life [9]. This study contributed to the growing body of evidence suggesting that hospitalized infants may thrive best in a quiet environment, with good nutrition, and consistent love and care from their parents, but without excessive stimulation and handling [6, 10, 11]. As first proposed by Bowlby in 1951 [12], the quality and quantity of the interaction between infants and their parents is particularly important to this concept. During the acute phase of NICU care, a variety of studies have reported that maternal presence, specifically through stimuli provided by voice and breast milk odor, results in more stable physiological responses [13, 14], improved oral feeding [15–18], fewer critical events [13, 19], and shorter length of stay [17, 18] for preterm infants. In the longer term, strong, responsive parent-infant interaction has been associated with improved behavioural outcomes in preterm infants [20–22], a relationship that may be inhibited by poor parental mental well-being [23–26]. As such, encouraging parental presence in the NICU, and providing parents with education and support to reduce their stress levels and improve their knowledge and confidence, is essential to improve preterm infant outcomes.

Building on the evidence from the literature and direct observation of the program in Estonia, we developed the Family Integrated Care (FICare) model specifically for the current Canadian NICU environment, to completely integrate parents into the NICU care team. The principle of FICare is that in the NICU, families should be supported, educated, and empowered to provide as much of their infant’s care as they are able [27, 28]. The FICare program includes a parent education program [29], a nursing education program [30], peer-to-peer support from ‘veteran’ parents [31], and adaptation of the unit policies, procedures, and other infrastructure as necessary, to provide social, psychological, and physical supports that enable greater parent participation.

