## Methods/Design

### Trial design

Due to the nature of the intervention, which involves changes to unit-level provision of care and interaction between participants, blinding of participants or NICU staff is not possible. Therefore, to avoid contamination of patients in the control arm, the cluster randomized controlled trial design was selected, in which level 3 NICUs were randomized but the intervention was targeted and the outcomes measured at the individual level. Presently, our prospective multi-centre cluster randomized controlled trial is being conducted at 19 tertiary level Canadian, 6 Australian, and 1 New Zealand NICU. The trial was designed, is being conducted, and will be reported according to the CONSORT 2010 guidelines for cluster randomized controlled trials [34]. Mount Sinai Hospital, where the pilot study of FICare was conducted, was assigned *a priori* to the intervention arm. Randomization was stratified by country, and within Canada was stratified by NICU size according to the number of yearly eligible admissions: < 200 (10 Canadian sites) or ≥ 200 (9 Canadian sites) admissions. Randomization of sites was performed using a random number generator. Enrollment in the trial commenced on 1^st^ April, 2013 and will continue until the required sample size of 675 infants in each arm is reached, which is estimated to occur in August, 2015.

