### Enrollment

Parental consent is being obtained from families of eligible infants at both the intervention and control sites. For NICUs randomized to the FICare intervention arm, the site program coordinator approaches parents of all potentially eligible infants soon after admission to the NICU to explain the study verbally and deliver an information leaflet detailing the purpose and process of the study, as well as any possible detrimental effects of participation. Parents are screened to determine if there are barriers to their participation in the trial, and informed of the FICare education sessions, which they may attend regardless of whether they participate in the trial. Parents are then approached for informed consent when their baby becomes eligible (i.e., stable on CPAP). Families are enrolled in the trial, after consent is obtained (Day 0). All families approached are recorded in a patient eligibility log regardless of actual participation. Infants whose parents decline to participate in the study receive standard care at that site.

For NICUs randomized to the control arm, the site program coordinator approaches the parents of all potentially eligible infants for consent to collect infant data and information on parental stress and anxiety. The families of eligible infants at control sites are not screened to determine whether they would be willing to spend at least 6 h per day in the NICU as per the FICare protocol. The infants of parents who consent are enrolled in the study once they meet the inclusion criteria, and continue to receive standard care.

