### Data collection

Data collection at both the intervention and control sites commences at enrollment and continues for the trial duration (21 days) and through to discharge from the NICU. Data collection utilizes the existing CNN database platform [36] in Canada, and in Australia and New Zealand, the Australian and New Zealand Neonatal Network (ANZNN) data system [37]. Data collected include demographics, antenatal and obstetric risks, delivery complications, admission illness severity scores, and selected practices and outcomes related to this trial. At each site, a trained research assistant abstracts data daily from patient charts directly into a laptop computer using a customized data entry program with built-in error checking and a standard manual of definitions. SSL-encrypted data are electronically transmitted directly from the Canadian sites to the CNN Coordinating Centre for verification and further cleaning. The Australia and New Zealand sites collate data via the ANZNN data verification system and submit encrypted data in batches to the CNN Coordinating Center.

Questionnaires and surveys are administered to parents by site program coordinators, and are available online and on paper. Data entered into online surveys are automatically included in a survey database and answers from paper documents are entered into the database by the program coordinator. In addition, in the Australia and New Zealand sites parents have the preferred option of entering answers directly via smartphone to a purpose-built web-based dataset that is being collated at the ANZNN Coordinating Centre.

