### Statistical analysis

The unit of analysis will be the individual infant, and all analyses will be based on the intention to treat principle. The distribution of baseline characteristics in the study population will be summarized at the individual and cluster level within each FICare and control groups, using descriptive statistical methods. The primary outcome of weight gain at 21 days post enrollment, will be compared between the FICare and control groups using Student’s *t*-test adjusted for the inflation factor (or design effect) with a minimum variation weight correction [46, 47] to account for intra-cluster correlation and imbalance of cluster sizes. In addition, a two-level hierarchical linear regression model will examine the primary outcome, accounting for clustering, and potential confounders including patient-level characteristics (birth weight, gestational age, small for gestational age, gender, multiple births, admission illness severity, caesarean section, chorioamnionitis, maternal hypertension or diabetes, maternal education, parity) and NICU-level covariates (NICU size, teaching institution).

Secondary outcomes will be compared between the FICare and control groups using similar methods including the Student’s *t*-test for continuous variables and the Chi-square test for categorical variables adjusted for clustering [50, 51], as well as hierarchical linear or logistic regression models, as appropriate. Furthermore, weight change over time will be examined longitudinally using multivariable multi-level hierarchical models to compare the rate of change in weight gain between infants from the two trial arms.

While we realize that multiple comparisons are a concern when more than one analysis of the data is performed, we are not interested in the joint confidence region for all of our hypotheses at once. Rather, we are interested in them one at a time. Under these conditions, Rothman and Greenland [52, 53] argue that “multiple inference procedures … are irrelevant, inappropriate and wasteful of information” because they produce improperly imprecise single intervals.

Prior to data unmasking and analyses, issues relating to missing data and potential sources of bias will be examined and appropriate correction methods determined.

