### Limitations and feasibility

A cluster randomized trial design was selected to evaluate FICare as it is an organizational and behaviour intervention where blinding of participants or investigators is not possible. Cluster randomized controlled trials are more effective at preventing contamination, but more susceptible to biases than trials randomizing individual subjects [54, 55]. In this trial, possible allocation bias is being minimized by the use of appropriate study design methods for cluster randomization including stratification (sites within each country randomized separately; big and small sites in Canada randomized separately) with randomization performed using a random number generator.

Selection bias may arise due to prospective recruitment of families after randomization of NICU sites, and differences in the nature and process of obtaining informed consent. Study coordinators who recruit families are not blinded to their site’s allocation and families consent to participate in rather than be randomized to the FICare intervention or control protocol. At intervention sites, consent is given to participate in the FICare program and to complete study questionnaires and collect infant data, whereas, at control sites consent is given for questionnaire completion and data collection only. Notably, the inclusion criteria at FICare sites require a time commitment of ≥ 6 h, whereas families at control sites are not specifically asked if they would be able to make the same commitment. As such, participants at intervention sites who commit to FICare may differ from those at the control sites, who do not have to commit to spending extended time in the NICU. For example, families who enroll in FICare may be at a higher socioeconomic level or have greater family support than control families.

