To assess selection bias, differences in the enrolment rate at FICare and control sites will be examined. Multivariable analyses will correct possible confounding bias by adjusting for baseline factors including social, economic (parental education, employment), demographic (maternal age, family size), obstetric (parity, pregnancy complications) and infant factors (gestational age, small for gestational age, illness severity at admission, and age at enrollment). Further analyses will consider propensity score methods accounting for imbalance of baseline characteristics between FICare and control groups [54]. While we will attempt to identify and adjust for all the possible confounding variables, we also acknowledge that any selection/participation bias could be due to some unmeasured element of “parent engagement” at the initiation of the intervention.

Subject attrition may also produce biased results and impact generalizability. Families in the FICare group are provided with as much physical, psychological and financial support as possible (including parent lounge; subsidized parking or a transit pass; access to peer-to-peer, social, and psychiatric support services), but no such supports are available to control families. Attrition bias will be minimized by performing statistical analyses according to the intention to treat principle. To minimize losses due to retro transfer from level 3 to level 2 units prior to completion of the 21-day trial period, the original study protocol has been amended to allow follow-up of these infants within level 2 units provided these units obtain Research Ethics Board approval, receive appropriate training, and comply with the study protocol including providing nurse education and parent education programs.

Possible bias due to differential withdrawal or study drop-out will be assessed by examining the distribution of baseline factors between families who consent and complete the study, and eligible families who consent and start but do not complete the study within the intervention and control sites. Furthermore, a sensitivity analysis will compare results from complete-case data and from all families who were enrolled where missing data are imputed using methods that account for clustering [56, 57].

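### Follow-up after transfer to a level 2 unit is conditional on that unit providing FICare components, so collection of the Day 21 primary outcome depends on delivery of the intervention

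*Protocol article*

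**What the plan says.** The rule is in Limitations and feasibility, in the paragraph on attrition. To reduce losses from transfers out of level 3 before the 21 days are complete, the protocol was "amended to allow follow-up of these infants within level 2 units provided these units obtain Research Ethics Board approval", and provided also that they "receive appropriate training, and comply with the study protocol including providing nurse education and parent education programs". The infants concerned are not limited to one arm.

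Other sections that bear on it:

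- Background and rationale names both education programs as parts of the intervention: "The FICare program includes a parent education program [29], a nursing education program [30".
- Enrollment says that control infants "continue to receive standard care". Limitations and feasibility adds that "at control sites consent is given for questionnaire completion and data collection only".
- Data collection, for both arms, "continues for the trial duration (21 days) and through to discharge from the NICU". No separate route to a weight recorded after transfer is described.
- Statistical analysis declares that "all analyses will be based on the intention to treat principle".
- Trial design gives the reason for randomizing units: "to avoid contamination of patients in the control arm, the cluster randomized controlled trial design was selected".

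**The concern.** Intention to treat requires the outcome to be sought for every enrolled infant, whatever care the infant goes on to receive. The amendment ties two separate matters together: whether a level 2 unit can continue the program, and whether the trial records a Day 21 weight there. An infant who goes to a unit without the programs falls outside the follow-up that the article describes. That infant is missing because of what the receiving unit delivers.

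The primary outcome is the change in weight z-score from enrollment to Day 21, so these infants would lack the endpoint itself. An intention-to-treat label governs how collected data are analysed; it cannot supply a weight that was not collected. If the share lost differs between arms, or if lost infants differ from retained ones to a different degree in each arm, the primary contrast is biased.

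**Working it through.** **1. Yardstick.** The point disputes no stated figure. The sample size section gives a target difference of 0.11 (25% of the control mean change: 0.25 × 0.42 = 0.105, rounded), SDs of 0.57 and 0.43, ICC 0.01, 80% power, 10% drop-out and 675 infants per arm. A two-sided test and 3 large plus 5 small sites per arm (half of the 16 sites) are assumed here.

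- Effective infants per arm: (0.57² + 0.43²)(1.960 + 0.842)² / 0.11² ≈ 331.
- With minimum-variance weights, site sizes in the ratio 315:113 and ICC 0.01: 625 per arm.
- With drop-out: 625 / 0.9 = 694, against 675 stated (2.8% apart).
- Power with 675 × 0.9 = 607.5 completers per arm: 79.4%.

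The stated size is reproduced closely enough.

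**2. Power is not the main issue.** With 10% loss in the FICare arm and an assumed 10%, 20%, 30% or 40% in control, power is 79.4%, 78.4%, 77.2% or 75.5%. The drop-out allowance covers lost precision. It does nothing about who is lost.

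**3. What the rule does in each arm.** The sentence can be applied in two ways.

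| Reading | FICare infants | Control infants |
|---|---|---|
| All conditions apply to both arms, as worded | Followed only where both programs are provided | Followed only where both programs are provided; otherwise lost |
| Education condition applies to FICare infants only | Followed only where both programs are provided | Followed under a lighter condition |

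On either reading, a FICare infant's Day 21 weight after transfer depends on continued delivery. On the second reading the hurdle is higher in the FICare arm. On the first, the hurdle is nominally equal, but a level 2 unit receiving control infants has no evident reason to run the programs, so loss could well be heavier among controls. The arm that loses more therefore depends on a reading that the text does not settle.

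**4. Form of the bias.** Let p be the share lost in an arm and δ the mean z-score change of lost minus retained infants. The complete-case mean equals the full mean minus p·δ. For FICare minus control:

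bias = p_C·δ_C − p_F·δ_F, which is (p_C − p_F)·δ if δ is the same in both arms.

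The documents give neither p nor δ. With assumed values:

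| Difference in loss | δ = 0.1 | δ = 0.3 |
|---|---|---|
| 5 points | 0.005 (5% of 0.11) | 0.015 (14%) |
| 10 points | 0.010 (9%) | 0.030 (27%) |
| 15 points | 0.015 (14%) | 0.045 (41%) |

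These are absolute values. The sign follows from which arm loses more and from the sign of δ, and both are unknown.

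**5. What the planned analyses can recover.** Under the rule, the FICare infants observed at Day 21 are those still in the NICU, those in level 2 units that provide the programs, and any others whose weight is obtained by a route not described. Imputation for the rest would rest mainly on infants whose program continued. It would tend to predict growth as if FICare had continued, which is not what intention to treat asks for. Weights before transfer help, but they describe growth before the care changed.

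**The case against.** The best defence has three parts.

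*The sentence is loose and condensed.* Compliance with the protocol at a control site means standard care; the Parent education program section places the sessions at intervention sites, and control consent covers questionnaires and data only. The education clause probably describes units that continue FICare. A reader might infer that the plan sends control infants into FICare-type units. The documents do not support that as an intention: contamination arises only if the unqualified wording is applied literally to control infants. This part stands, but it does not rescue the rule for FICare infants.

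*The full amendment is not shown.* It may set conditions by arm or provide for retrieving weights alone, and the article does not say outright that no weight is sought elsewhere. That is fair. However, the article is not silent: it states a condition on follow-up, offered as the remedy for losses, and that condition is the wrong one.

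*Missing data are provided for.* Infants scheduled for early transfer are excluded. Completers and non-completers are to be compared within intervention and control sites. A sensitivity analysis imputes missing data with allowance for clustering. Missing-data issues are to be examined before unmasking, weight is modelled longitudinally, and residual bias is to be reported. These measures reduce the number affected and the likely harm. The comparison diagnoses the loss without recovering outcomes, and the imputation is a sensitivity analysis with the limit shown in the working.

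A reader might also suppose that transferred infants are the stable, well-growing ones, and so predict the direction of bias. No section describes their growth, so that step is not available.

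**Conclusion.** The point holds. As the article states the rule, recording the primary outcome after transfer depends on delivery of intervention components. Missingness can therefore differ by arm, in conflict with the intention-to-treat principle that the article declares. This rests on the wording alone.

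The size and direction are not established. The 0.005 to 0.045 range illustrates how the bias scales; it is not an estimate, and its upper end needs both extreme assumptions together. It also takes δ as equal in the two arms. Only infants transferred before Day 21 are affected, and their number is not given, though it was enough of a concern to prompt an amendment. Control contamination is a risk of the wording, not a demonstrated feature of the design.

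**What to change.** Separate outcome collection from intervention delivery.

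1. **Outcome.** Seek the Day 21 weight from the level 2 chart for every transferred infant in both arms, whether or not the unit is trained or provides the programs, subject to data-only ethics or data-release approval. Analyse each infant in the NICU and arm of enrollment.
2. **Intervention.** State that the training and education conditions apply only to continuing FICare for intervention-arm infants, and not to follow-up of control infants.

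If the full amendment already does this, only the article's sentence needs correcting.

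The cost is extra approvals and chart requests to level 2 units, some of which may not be obtainable, so some weights will remain missing. Some FICare infants with shortened exposure will stay in the analysis, which may dilute the contrast; intention to treat accepts that.

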## Discussion

In this age of accountability, infant outcomes, parental mental health, and reduction of health care costs are important objectives. The FICare program addresses all these issues because it can potentially improve infant outcomes, decrease parental stress and anxiety, and reduce resource use including duration of oxygen therapy and length of hospital stay with potential per diem cost savings. Improvement of neonatal outcomes by FICare may lead to reduced mortality and morbidity post-NICU discharge. In addition, FICare aims to increase the confidence and capability of parents to care for fragile preterm infants when they go home, which may reduce the need for post-discharge support for families, outpatient clinic visits, re-hospitalizations, and other health care utilization. Future studies are required to examine the longer-term effects of FICare. Additional trials may be conducted to assess the feasibility, safety, and efficacy of expanding the FICare model of care to NICU infants who are more acutely ill, such as those on a mechanical ventilator or who require surgery. If effective, the FICare model could represent a paradigm shift in approach to health care that may be applicable to other areas such as pediatrics, palliative care, geriatrics and chronic care.

## Abbreviations

BPD: bronchopulmonary dysplasia
CNN: Canadian Neonatal Network
CPAP: continuous positive airway pressure
FICare: Family Integrated Care
ICC: intra-cluster correlation coefficient
IVH: intraventricular hemorrhage
NEC: necrotizing enterocolitis
NI: nosocomial infection
NICU: neonatal intensive care unit
PIPEDA: Personal Information Protection and Electronic Documents Act
PSS:NICU: Parental Stress Survey: Neonatal Intensive Care Unit
ROP: retinopathy of prematurity
STAI: State Trait Anxiety Index
